### Secondary objective analysis

A.ANOVAs will be used to compare the following two-year outcome measures between the two groups: ASES, EQ-5D-5 L, PROMIS and IPAQ. In addition, the incidence proportion of complications will be derived for each group, and a comparison of the two groups will be conducted for re-operation, infection, nerve injury, hematoma, hospital readmission, and intra-articular screw penetration using a chi-square analysis. Logistic regression modeling will be used to account for variables demonstrating group imbalance.B.The incidence of malunion, non-union, and osteoarthritis will be compared between groups using chi-square statistics (and odds ratios). Time to union will be determined with Kaplan-Meier curves with a log rank test for group comparisons.C.The degree of association between the degree of displacement and angulation of the fracture fragments and the Constant score will be determined. Multivariable regression analysis will be carried out to determine if an association exists between fracture angle and the degree of displacement (independent variables), and functional outcomes using the Constant score (dependent variable). If such an association is identified, area under the curve plots will be used to determine at what degree of angulation or displacement a particular treatment is indicated.D.The degree of association between the quality of surgical reduction [degree of displacement/angulation] of the fragments based on post-operative CT scan and the Constant functional outcome measure will be determined in the surgical group using a multivariable regression analysis.

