### Secondary objectives

A.Is there a difference between non-operative management and locking plate surgical fixation of low-energy displaced three- and four-part proximal humerus fractures in the elderly population based on the ASES functional outcome score [47], the short form Patient Reported Outcomes Measurement Information System (PROMIS) upper extremity score [48], the International Physical Activity Questionnaire (IPAQ) for the elderly [49], and the EuroQol EQ-5D-5 L Health Questionnaire Quality of Life (QoL) functional outcome score [50] over a 2-year follow-up period? What is the incidence of complications of non-operative management and locking plate surgical fixation of low-energy displaced three- and four-part proximal humerus fractures in the elderly population based on infection, nerve injury, intra-articular screw penetration and bleeding (hematoma), reoperation rate, or hospital readmission over a 2-year follow-up periodB.Does a difference exist between non-operative management and locking plate surgical fixation of low-energy displaced three- and four-part proximal humerus fractures in the elderly population based on radiographic outcomes including time to union, non-union, malunion, and joint arthrosis?C.Does the degree of initial displacement or angulation of the fracture fragments correlate with final functional outcome measures?D.Does the quality of the surgical reduction correlate with final functional outcome measures?

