### Purpose and hypothesis

The main purpose of this trial is to determine whether or not a functional difference exists between operative and nonoperative management of low-energy displaced three- and four-part proximal humerus fractures as measured by the Constant, (PROMIS) upper extremity score, the International Physical Activity Questionnaire (IPAQ) for the elderly, and the EuroQol EQ-5D-5 L Health Questionnaire Quality of Life (QoL) functional outcome score [46, 48–50] over a period of 24 months. We will also aim to determine which method of treatment is associated with a higher incidence of complications as well as the time to union of malunion, nonunion and joint arthrosis. Lastly, we will determine whether initial displacement or quality of surgical reduction has an impact on functional outcome.

We hypothesize that there will be no statistically significant difference in functional outcomes between operative and nonoperative methods. We also hypothesize that there will be a greater incidence of complications in the operative group. Lastly, we hypothesize that fractures with a greater Neer classification and those with a greater degree of initial displacement will have worse functional outcomes.

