### Sample size calculation

The sample size will be 160 patients. The minimum clinically important difference for the Constant score is 12 [52, 53], with standard deviation of 23.1 from measurements in previous studies of similar patient populations. For the primary outcome, to achieve 80% power to detect a clinically meaningful difference of 12 points on the Constant score, with standard deviation of 23.1, and alpha of 0.05, a sample size of approximately 116 people would be necessary (58 per arm). The overall sample size is increased from 116 to 129 to account for an expected 5% crossover from the non-operative study arm to the operative study arm. An additional 31 patients were added for a conservative sample size adjustment accounting for 20% loss-to-follow-up over the two years of follow-up, for a total sample size of 160 patients.

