### Outcome measures

Outcome measures are separated into primary and secondary as outlines below. All functional assessment scores will be completed at baseline and 3, 6, 12 and 24 months post injury. Complications and adverse events will be recorded on standardized case-report forms that will be completed immediately following the completion of the surgical procedure for patients randomized to the surgical treatment arm. At follow-up visits, clinical evaluation will be conducted to monitor for complications including infection, nerve injury, and hematoma formation or hospital re-admission.

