### Statistical analysis

Patient characteristics will be summarized with descriptive statistics. Comparative analyses will be based on the full trial cohort, using the intention-to-treat (ITT) principle (i.e., based on the participant’s randomized allocation). Reasons for missing data will be examined, and appropriate imputation methods will be used to address missing follow-up data, retaining the entire cohort for the ITT analysis. Interim analyses will occur for primary outcome measure when 50% of recruited patients finish their 1-year follow-up. Using the O’Brien-Fleming criteria for sequential tests, the significance level will be 0.005 for the interim analysis and 0.049 for the final analysis. The O’Brien-Fleming boundaries, as well as clinical judgment concerning adverse events, will be used as guidelines for stopping the study early. However, this interim analysis will only occur if randomization is not yet complete.

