### Primary objective analysis

A.The analysis involves a comparison of the mean Constant scores between the two groups on an intention-to-treat basis. An ANOVA will be used to assess whether there is a statistically significant difference between treatment groups for the mean Constant scores at 2 years, with stratification factor included. A non-parametric Kruskal-Wallis will be instead used if parametric tests are not justified. In addition, a Generalized Estimated Equations (GEE) analysis will be conducted to determine whether there is an effect over time (repeated measures) (i.e. pre-operatively, 3, 6, 12 and 24 months follow-ups).

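### The four secondary functional scores have a stated between-arm comparison at two years only, although the objective spans the two years and the Constant score also gets a repeated-measures analysis

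*Protocol article*

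**What the plan says.** All places are in the protocol article.

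- **Secondary objectives (A)** asks whether the arms differ on ASES, PROMIS, IPAQ and "EuroQol EQ-5D-5 L Health Questionnaire Quality of Life (QoL) functional outcome score [50] over a 2-year follow-up period".
- **Purpose and hypothesis** puts the Constant, PROMIS, IPAQ and EQ-5D-5L in the main purpose of the trial, again with a period rather than a point in time: "functional outcome score [46, 48–50] over a period of 24 months".
- **Outcome measures** sets the schedule: "All functional assessment scores will be completed at baseline and 3, 6, 12 and 24 months post injury".
- **Secondary objective analysis (A)** fixes the comparison: "ANOVAs will be used to compare the following two-year outcome measures between the two groups: ASES, EQ-5D-5 L, PROMIS and IPAQ".
- **Primary objective analysis** compares the Constant score at two years by ANOVA and then adds: "a Generalized Estimated Equations (GEE) analysis will be conducted to determine whether there is an effect over time (repeated measures". The visits listed there are pre-operative and 3, 6, 12 and 24 months.
- **Statistical analysis** says of missing data: "appropriate imputation methods will be used to address missing follow-up data, retaining the entire cohort for the ITT analysis". It names no imputation method.
- **Sub-analysis** plans subgroup, osteoarthritis-progression and prognostic analyses. It plans no longitudinal comparison of the secondary scores.

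**The concern.** The objective is worded over a period and the data are collected over that period, but the one named test looks at its end. For the Constant score, the same objective wording and the same schedule lead to an end-of-study test plus a repeated-measures analysis. For the other four scores only the end-of-study test is named.

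The course of recovery matters when surgery is compared with sling treatment in patients over 60. One arm might regain function or quality of life sooner and the other catch up by 24 months. The stated comparison of ASES, EQ-5D-5L, PROMIS and IPAQ would then show no difference, which is also what the trial hypothesises for function. A reader could take that as equal recovery when it shows only equal end states.

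The second issue is dropout. A patient who gives scores at 3, 6 and 12 months and then leaves has no value for a two-year ANOVA. That patient enters only through the imputation, whose method is left open.

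**Working it through.** **The plan's own figures.** The article gives no power or precision figure for the secondary scores. Its sample size concerns the Constant score (difference 12, SD 23.1, 80% power, alpha 0.05, taken as two-sided). The normal formula gives 2 × (1.960 + 0.842)² × 23.1² / 12² = 58.17 per arm, against the stated 58. That figure is not in dispute and this point does not touch it.

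**Objective, schedule and analysis side by side.**

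| | Constant | ASES, EQ-5D-5L, PROMIS, IPAQ |
|---|---|---|
| Objective worded over two years | yes | yes |
| Collected at 3, 6, 12, 24 months | yes | yes |
| ANOVA at two years | yes | yes |
| Repeated-measures analysis over visits | yes (GEE) | none stated |

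The columns differ only in the last row.

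**Count.** Four scores at four follow-up visits make 4 × 4 = 16 score-by-visit combinations. The stated ANOVAs cover 4 × 1 = 4. The remaining 12 (3, 6 and 12 months) have no stated between-arm comparison.

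**Dropout.** The sample size section allows for 20% loss over two years. Of 160 patients, 0.20 × 160 = 32 could lack a 24-month value. How many of them would have earlier scores is not given. The number may be smaller for questionnaires, because the article mails them to patients who choose not to return.

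**What a repeated-measures model gains in precision.** Assume equal variance at each visit and equal correlation ρ between visits; the article gives neither. The variance of a four-visit average difference, relative to a single-visit difference, is (1 + 3ρ)/4.

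- ρ = 0.5: ratio 0.625, SE ratio √0.625 = 0.79, SE 21% smaller.
- ρ = 0.7: ratio 0.775, SE ratio √0.775 = 0.88, SE 12% smaller.
- Over the wider range ρ = 0.3 to 0.8, the variance ratio runs from 0.475 to 0.85.

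These figures belong to the average over four visits. With complete data and a treatment-by-visit term, the 24-month contrast is essentially the one the single-visit analysis gives, so the 12–21% does not carry over to it.

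**The case against.** The case for leaving the plan as it is has five parts.

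1. **The wording is ambiguous.** A phrase about a two-year period can simply state the length of follow-up. The primary objective uses it with a 24-month endpoint, and objective A uses it for complications, where it is the observation window. A reader might infer that the stated analysis cannot answer the stated objective. The text does not force that reading: if only length of follow-up is meant, the two-year ANOVA does answer it. Against this, the same wording for the Constant score is matched with an analysis over all visits.
2. **Silence is not exclusion.** The article does not rule out other analyses, and a statistical analysis plan may add them. Earlier scores could also inform the imputation. A reader might infer that three quarters of the follow-up data are discarded or that early differences are never tested. The document supports only that no comparison of them is stated. It does, however, name both the method and the time point, so this is more than a detail left open.
3. **Early function is partly covered.** The GEE for the Constant score addresses the course of shoulder function, so early recovery is not wholly untested. That stands, and it narrows the gap to patient-reported function, physical activity and quality of life. The article itself says the Constant score gives more weight to range of motion and strength.
4. **The precision gain is for another quantity.** This stands in full, as shown in the working.
5. **One time point is a legitimate choice.** It matches the primary endpoint and keeps the number of tests low. This stands too, and it is why 24 months should remain the main secondary estimate.

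**Conclusion.** The point holds in a limited form. For ASES, EQ-5D-5L, PROMIS and IPAQ, the article states a comparison at two years only, while its objective, its collection schedule and its own treatment of the Constant score point to an analysis across visits. Twelve of 16 score-by-visit combinations have no stated between-arm comparison. A recovery difference that closes by 24 months would not be picked up on these scores, and patients lost before 24 months would count only through an unspecified imputation.

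The count follows from the text alone. The view that the objective concerns the whole period rests on the more natural but not the only reading of its wording. The conclusion does not rest on any assumed correlation. It concerns secondary outcomes and is worth correcting because the remedy is cheap and already used in this trial; it casts no doubt on the primary comparison.

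**What to change.** Extend the repeated-measures approach of the primary objective analysis to the four secondary scores. Fit one model per score over 3, 6, 12 and 24 months, with terms for treatment, visit, treatment-by-visit and the fracture-type stratum. Name the 24-month difference as the main secondary estimate, and report the 3-, 6- and 12-month differences with 95% confidence intervals as supportive. State how this model and the planned imputation fit together, so that it is clear how observed scores from patients who later drop out are used. Make no claim of a smaller standard error at 24 months beyond that use.

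If only an end-of-study comparison is intended, reword secondary objective A and the purpose statement for these scores to say at two years. That makes the text consistent but leaves the recovery period without a stated comparison.

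**Cost:** a few sentences and modest analysis work, with no new data or visits. The downside is 4 × 3 = 12 further estimates beside the four at 24 months; the multiplicity is handled by labelling them supportive.

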Previous comparisons of non-operative and locking plate fixation have been conducted with no clear consensus as to the optimal management of osteoporotic proximal humerus fractures. No difference in the quality adjusted life years (QALYs) and societal costs between the two treatment options have been demonstrated [43]. In a randomized control trial evaluating 60 displaced 3-part proximal humerus fractures, Olerud et al. found no statistically significant difference in functional outcomes (Constant, Disability of the Arm Shoulder and Hand (DASH), and health-related quality of life (HRQoL) scores) between non-operative management and locking plate fixation over a 2-year period. One patient (3%) in the non-operative group went on to require surgical intervention and 9 patients (30%) in the locking plate group had a secondary operation with a major complication rate of 13% [44]. Fjalestad and Hole have recently reported on 50 elderly patients with displaced proximal humerus fractures randomized to non-operative or operative management using locking plate fixation. Fracture patterns were categorized based on the AO/OTA classification system, which makes a direct comparison to the study by Olerud et al. difficult. With the Constant score as their primary outcome, Fjalestad and Hole found no significant functional or HRQoL difference over a 2-year follow-up period. Similar to previous studies [25, 26], a 35% overall complication rate with surgical management was reported [45]. Both randomized control trials were limited by a small number of enrolled patients [44, 45].

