### Interventions

#### Non-operative treatment

Treatment will consist of sling immobilization for a period of 6 weeks. Patients will remain in a shoulder immobilization sling for 6 weeks with range of motion of the elbow, hand and wrist with addition of pendulum exercises from 3 weeks. Active mobilization will occur after 6 weeks. Light activity and range of motion in physiotherapy will be permitted at this time. Restrictions will be lifted and full function permitted once range of motion and strength have recovered.

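### The hypothesis of more complications after surgery has no stated between-arm estimate: the plan compares only six single items, and one of these needs an implant

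*Protocol article*

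**What the plan says.** All of this is in the protocol article.

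- **Purpose and hypothesis** sets a comparative aim, to "determine which method of treatment is associated with a higher incidence of complications", and a directional hypothesis that "there will be a greater incidence of complications in the operative group". Both speak of complications as one quantity.
- **Secondary objectives (A)** asks for the incidence of complications "based on infection, nerve injury, intra-articular screw penetration and bleeding (hematoma), reoperation rate, or hospital readmission". That makes six items.
- **Secondary objective analysis (A)** says that "the incidence proportion of complications will be derived for each group, and a comparison of the two groups will be conducted for re-operation, infection", followed by nerve injury, hematoma, "hospital readmission, and intra-articular screw penetration using a chi-square analysis". These are the same six items. Part B of that section adds chi-square comparisons of malunion, non-union and osteoarthritis, again one by one.
- **Non-operative treatment**: "Treatment will consist of sling immobilization for a period of 6 weeks". No implant is used. Other radiographic outcomes classes screw penetration as hardware failure.
- **Sample size calculation** allows for an "expected 5% crossover from the non-operative study arm to the operative study arm". Compliance and loss of follow-up keeps crossovers in their randomized group.

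**The concern.** The hypothesis is about one incidence, but the stated comparison covers six components. The overall proportion will be available for each arm, yet no contrast between the arms is attached to it, and no rule says which of the six results would confirm or refute the hypothesis.

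This can mislead in two directions. An excess spread thinly over several items may leave each test non-significant. Conversely, a few screw penetrations may give p < 0.05 and seem to support the hypothesis, although almost only plated patients can have the event.

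The authors expect no functional difference, and the Discussion presents avoiding unnecessary surgery as a benefit to patients and to cost. If function does prove similar, the complication comparison will carry much of the treatment decision.

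**Working it through.** **Plan's own figure.** The article gives no sample size or power for complications. The total is 160 at 1:1, so 160 / 2 = 80 per arm, or 80 x 0.8 = 64 per arm after the allowed 20% loss. Power below is the exact power of the uncorrected two-sided 0.05 chi-square test; intervals are Newcombe 95%.

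**1. Screw penetration.** Patients at risk in the non-operative arm: 0.05 x 80 = 4 crossovers. Assume 4 events in 80 operative and 0 in 80 non-operative patients. The expected count is (4 + 0) / 2 = 2 per arm. Chi-square gives p = 0.043; Fisher's exact test gives p = 0.12. The named test and the exact test fall on opposite sides of 0.05.

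**2. Events concentrated in one item.** Under Surgical fixation of displaced fractures, one cited trial of 3-part fractures reports a second operation in 9 patients (30%) after plating and surgery in 1 (3%) after non-operative care. Taking 30% v 3.3% for the re-operation item, power is 99.9% with 80 per arm and 99.4% with 64. With the plating review's 13.8% re-operation rate against 3.3%, it is 68% and 60%. With 13.8% against the 5.6% eventual operation rate of the largest non-operative study, it is 42% and 35%.

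**3. Events spread evenly over six items.** For surgery, take the rate in the statement that "a 35% overall complication rate with surgical management was reported"; for non-operative care, take the 13% of the non-operative review.

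- Pooled: 0.35 x 80 = 28; 0.13 x 80 = 10.4, taken as 10. Difference 28/80 - 10/80 = 22.5 points (9.4 to 34.8), p = 0.0008. Power at 35% v 13%: 92% (80 per arm), 85% (64).
- Per item, assuming one event per patient: 35/6 = 5.8% v 13/6 = 2.2%, about 5 v 2 patients. 5/80 v 2/80 gives p = 0.25; power 19% (80 per arm), 16% (64).

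**4. The only overall rates in the article that come from both arms of one trial.** These are 24% surgical and 18% non-surgical: 0.24 x 80 = 19 v 0.18 x 80 = 14. Difference 6.25 points (-6.4 to 18.7), p = 0.33. Power at 24% v 18% is about 15% with 80 per arm and 13% with 64.

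| Scenario, 80 per arm | Test | Power |
|---|---|---|
| 30% v 3.3%, re-operation | single item | 99.9% |
| 13.8% v 5.6%, re-operation | single item | 42% |
| 35% v 13%, even spread | single item | 19% |
| 35% v 13% | pooled | 92% |
| 24% v 18% | pooled | about 15% |

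**The case against.** The strongest reply is that the six tested items are exactly those that Secondary objectives (A) lists, so objective and analysis match. On this view, ranking secondary tests or adding an interval is detail that an article leaves to the full plan. The match is real, but it does not reach the hypothesis, which concerns a single incidence. The article itself fixes the hypothesis, the derived quantity, the tested items and the test, and these do not connect. A generous reader could extend the comparison to the total, but the sentence attaches it to the listed items.

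A reader might infer from 19% against 92% power that the planned tests would generally miss a true excess. The article does not support that:

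- The even spread is an assumption, and the re-operation figures in the article's own Background point to concentration in one item.
- The 13% fits the six items poorly. Of 650 patients in that review, 44 had varus malunion and 13 avascular necrosis: 57/650 = 8.8 of the 13 points lie outside the six items, and malunion is compared separately in part B. About half of those fractures (49%) were also undisplaced or one-part, whereas this trial enrols displaced 3- and 4-part fractures.
- At 24% v 18% the pooled test would also usually be non-significant.

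A reader might also infer that the screw penetration comparison is invalid. Under intention to treat, a harm specific to one strategy is a genuine part of the difference between strategies. The objection is narrower: equal rates are not a meaningful null for that item alone. The same reasoning applies to any composite that includes it, so the composite must be shown with and without it.

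**Conclusion.** The point holds. The article states a directional hypothesis on overall complication incidence and names no between-arm estimate for it. One of its six component tests is uninformative by design, and its named method is unreliable at the counts to be expected.

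The size of the loss is not fixed. It is near nil if complications concentrate in re-operation at 30% v 3%, and considerable if they spread over the items. At 24% v 18% the gain is an interval, not a significant test. The rates come from studies with different case mix and definitions, and the 4 v 0 count is assumed, so the figures illustrate rather than predict.

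This is a secondary objective. The Constant score analysis is unaffected, no data are lost, and the incidence per arm is already planned. The change is still worth making because it costs almost nothing.

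**What to change.** In Secondary objective analysis (A):

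1. Name as the analysis of the complication hypothesis the proportion of patients with at least one of the six complications listed under Secondary objectives (A), by randomized arm, as a risk difference with 95% CI.
2. Repeat it without screw penetration, to show how far plate-only events drive the result.
3. Report the six items per arm as counts and proportions with intervals. Report screw penetration among plated patients, without a between-arm test.

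The cost is a few sentences, with no new outcome, data collection or patients. The drawback is that one proportion mixes mild and severe events, so the individual items must stay beside it.

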### Non-operative treatment of displaced fractures

Non-operative management of proximal humerus fractures with a period of immobilization and progressive physiotherapy is a simple, noninvasive and readily available treatment option. In a systematic review of non-operative management, Iyengar et al. [9] evaluated 12 studies (*n* = 650) [10–21], with a mean age of 65.0 years and a mean follow-up of 3.8 years (range of 1–10 years). Based on the Neer classification [22], there were 49% undisplaced or one-part (*n* = 317), 25% two-part (*n* = 165), 21% three-part (*n* = 137), and 5% four-part (*n* = 31) fractures. Although variable, all treatment protocols included a period of sling immobilization followed by progressive mobilization as tolerated. The mean rate of radiographic union was 98% (range 93–100%). Various functional outcome scores were used; with 6 studies (*n* = 272) [10, 12, 14, 19–21] showing a weighted mean Constant score of 74 (range 55–81) corresponding to a “fair” outcome. Across all studies, a 13% complication rate was reported, with varus malunion being the most common (*n* = 44 or 7%). Proximal humerus avascular necrosis was found to be uncommon (*n* = 13 or 2%) [9]. In the largest included trial, Hanson et al. reported the functional outcomes of non-operative management through a prospective evaluation of 160 patients, with 124 patients having complete 1-year follow-up. Nearly half (53.1%) were undisplaced fractures. The average Constant score was 74.3 with a mean difference between the injured and contralateral shoulder of 8.2. They found an estimated median time to definitive union of 14 weeks, and a 7% risk of delayed or nonunion. Four patients went on to require surgical fixation and 5 patients underwent arthroscopic decompression, with an eventual operation rate of 5.6% [12]. With a large focus on undisplaced fractures, these studies highlight that non-operative management of proximal humerus fractures can lead to satisfactory functional outcomes with modest complication rates. In a report of non-operative management of displaced proximal humerus fractures, Yuksel et al. reported a mean Constant score of 61.3 (*n* = 18, eight 3-part and ten 4-part; mean age of 68.2 years; mean follow-up of 3.3 years), with nonunion and osteonecrosis detected in 27.8% (*n* = 5) [23].

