### Surgical fixation of displaced fractures

Displaced proximal humerus fractures are commonly treated with open locking plate fixation [4–6, 8, 24–26]. A systematic review of 514 displaced proximal humerus fractures treated with locking plate fixation (12 included studies, average age of 62, average follow-up of 2.4 years) [27–38] showed an overall healing rate of 96.6%. The review included 34.0% two-part (*n* = 175), 44.7% three-part (*n* = 230), and 21.2% four-part (*n* = 109) fractures. Nine out of the 12 studies (*n* = 376) [27–29, 32, 33, 35–38] reported an average Constant score of 73.6 when evaluating functional outcome. When stratified for fracture classification, the Constant score was significantly less for 4-part fractures in comparison to the 2-part fractures (*p* = 0.02). The overall complication rate was 48.8% with a reoperation rate of 13.8%. With the exclusion of varus malunion, the complication rate remained high at 32.6% over the 12 studies analyzed [24]. Two other multicenter studies evaluated locking plate fixation for the treatment of displaced proximal humerus fractures reported similar Constant scores of 70.6 and 72 at a minimum of 1 year follow-up, and overall complication rates of 40 and 45% [25, 26]. The Proximal Fracture of the Humerus Evaluation by Randomisation (PROFHER) trial was another multi-centered randomized controlled trial of 250 patients > age 16 which showed no difference between operative and nonoperative management using the Oxford shoulder score and the Short Form 12 (SF-12). The complications in the surgical and nonsurgical group were reported as 24% and 18% respectively [39].

Despite the lack of superiority demonstrated, there has been a significant increase in surgical fixation of proximal humerus fractures following the introduction of locking plate technology over the last decade [40, 41]. Associated with high complication rates, open reduction and internal fixation of isolated proximal humerus fractures in the elderly has also been found to be an independent risk factor for inpatient adverse events and mortality [42].

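### The hypothesis of more complications after surgery has no named test: the plan compares six single items and gives no rule that links them to overall incidence.

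*Protocol article*

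**What the plan says.** Under Purpose and hypothesis, the protocol article sets out to "determine which method of treatment is associated with a higher incidence of complications" and then commits to a direction: "We also hypothesize that there will be a greater incidence of complications in the operative group". Both statements concern one quantity, the incidence of complications in each arm.

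Item A of the Secondary objectives defines that incidence by a list: "based on infection, nerve injury, intra-articular screw penetration and bleeding (hematoma), reoperation rate, or hospital readmission". Item A of the Secondary objective analysis says that "the incidence proportion of complications will be derived for each group", and then that "a comparison of the two groups will be conducted for re-operation, infection, nerve injury, hematoma, hospital readmission, and intra-articular screw penetration using a chi-square analysis". The six items are the same in both places. The next sentence provides for logistic regression where groups are imbalanced, but it does not name the outcome to be modelled.

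Malunion and non-union are handled under item B of the same section, each compared by chi-square with odds ratios.

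**The concern.** The hypothesis is about overall incidence, but the only comparisons named in item A are item by item. The overall proportion gets no test, effect measure or confidence interval, and nothing says what pattern across six results would support or fail to support the hypothesis. The results would then have to be interpreted after they are known.

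Two features make this more than a matter of style. With six chances, a significant item against surgery can appear when the overall risks are equal. And screw penetration in practice needs a plate, so that item can only go against surgery.

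The Discussion cites surgical complications as a reason to avoid unnecessary surgery. If function does not differ between arms, the complication result will carry much of the trial's message.

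**Working it through.** **Inputs from the article.** Total 160, allocated 1:1, gives 80 per arm. With the planned 20% loss, 160 × 0.80 / 2 = 64 per arm. Alpha is 0.05, taken as two-sided because the sidedness is not stated. Reported complication rates in the randomized trial of 250 patients cited in the Background: 24% surgical, 18% non-surgical.

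**The plan's own figure.** The article gives no power or sample size figure for complications. Its primary-outcome calculation is broadly reproducible: 2 × (1.960 + 0.842)² × (23.1/12)² ≈ 58.2 per arm (58 stated); 116 / 0.95² = 128.5, rounded up to 129; 129 + 31 = 160. The arm sizes above can be used.

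**Assumptions of mine.** Equal overall risk of 30% in both arms; six independent items of equal risk; Pearson chi-square without continuity correction.

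**Step 1, item risk.** 1 − (1 − 0.30)^(1/6) = 0.0577 per item.

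**Step 2, one item.** Exact enumeration of the two binomials gives the chance of a result significant against surgery: 0.0238 at 64 per arm and 0.0208 at 80 per arm.

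**Step 3, at least one of six.**
- 64 per arm: 1 − (1 − 0.0238)^6 = 0.135
- 80 per arm: 1 − (1 − 0.0208)^6 = 0.119

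The large-sample value is 1 − 0.975^6 = 0.141.

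**Step 4, one overall test.** The same enumeration at 30% in both arms gives 0.026 against surgery at either size.

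**Step 5, screw penetration alone.** With 4 events against 0, the chi-square statistic is 4.13 (64 per arm) or 4.10 (80 per arm), above the critical value of 3.84; with 3 against 0 it is 3.07 or 3.06. Four events are therefore enough. With an assumed true rate of 5% to 10% in the operative arm and 0% without a plate, four or more events occur with the following chances:

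| Per arm | 5% | 8% | 10% |
|---|---|---|---|
| 64 | 40% | 76% | 89% |
| 80 | 57% | 89% | 96% |

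**Step 6, power of the single overall test.**

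| True rates (operative vs non-operative) | 64 per arm | 80 per arm |
|---|---|---|
| 24% vs 18% (cited randomized trial) | 13% | 15% |
| 35% vs 13% (rates from two different Background sources) | 84% | 91% |

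**Use of the word 'complication'.**
- Secondary objectives, Purpose and hypothesis, and Secondary objective analysis keep malunion and non-union apart from complications.
- The Abstract lists them together with "other" complications.
- The Background counts varus malunion as a complication in both cited reviews. For non-operative care, "a 13% complication rate was reported, with varus malunion being the most common". For plating, the rate is 48.8% with it and 32.6% without.

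**The case against.** Much can be said for the plan. The tested list matches objective A exactly, and the paragraph that holds the hypothesis names malunion and non-union separately from complications. A reader might infer that these two outcomes go untested. They do not: item B compares both. The broader usage in the Background belongs to cited reviews. Keeping surgical and medical complications apart from radiographic union is a legitimate choice.

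A reader might also infer that any one significant item would confirm the hypothesis. The article does not say so; the risk comes only from the absence of a rule. Nor should the six tests be charged with a false-positive rate of 25% (64 per arm) or 23% (80 per arm) in this scenario. Those figures count significance in either direction, and an item that favours surgery cannot support a hypothesis directed against it. An argument about power lost to a Bonferroni correction, or about bias in a pooled test of listed complications, would address procedures that the plan does not contain.

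The full protocol or analysis plan, not shown, may define a composite. That limits the weight of the point but does not remove it: the article does specify how complications are to be compared, and what it specifies does not answer its own hypothesis.

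**Conclusion.** The point holds in a limited form. The analysis stated for complications does not test the hypothesis stated for them, and no rule links the two. When the true overall risks are equal, the chance of at least one item significant against surgery is about 13% (64 per arm) or 12% (80 per arm), against about 2.6% for one overall test.

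These figures rest on an assumed 30% risk spread evenly over six independent items. Re-operation, infection and readmission probably overlap, which would lower the 13% and 12%. In the other direction, screw penetration is not balanced between arms even when overall risks are equal, and that scenario leaves this out. The rates used for that item are assumed.

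The documents do not support a claim that malunion and non-union are left out of the analysis. What they show is two usages of one term, which should be settled. This concerns a secondary hypothesis and leaves the primary analysis untouched. It is a cheap improvement.

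**What to change.** In item A of the Secondary objective analysis:

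1. Name one per-patient comparison, any complication within 24 months on the objective A list, as the test of the hypothesis. Report the risk difference with a 95% confidence interval, adjusted for fracture type (3- or 4-part), the stratification factor.
2. Present the six item comparisons as descriptive estimates with confidence intervals. Screw penetration then counts as a harm of surgery within the composite without deciding the hypothesis alone.
3. State whether malunion and non-union count as complications, and use the term in that sense throughout. Report a second version of the composite that adds both, read from the plain films taken in both arms. Post-treatment CT is planned only after surgery and would make ascertainment unequal.

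The cost is wording only, since every item is already collected. There are two downsides. A composite mixes events of different severity, so the components must still be shown; malunion in particular could dominate the second version, which is a reason to keep it out of the first. And at 24% against 18% the overall test has only 13% to 15% power, so the interval will be more informative than the p-value.
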